#### Rationale for parasite genotyping

RTS protein is derived from a sporozoite surface antigen of the *P. falciparum* strain NF54. In the efficacy study conducted in Gambian men under conditions of natural challenge, protection was not limited to the NF54 parasite genotypeError: Reference source not found. In this study, ***samples for the determination of parasite strain will be collected from Cohorts 1 and 2 for all efficacy endpoints to allow for the possibility of evaluating strain-specific efficacy*** ~~protection against infection due to multiple strains will be assessed in the children in Cohort 2~~. Parasites  ~~from the first parasite-positive sample for each child~~ will be characterised at the Th2R and Th3R epitope sequences of the gene encoding the circumsporozoite protein. **(Amended August 13, 2002) (Amended January 17, 2003)**

#### Rationale for sample size for the primary endpoint

Although trials are often powered to detect differences between vaccinated and unvaccinated, the decision to proceed with the clinical development plan is conditional on the vaccine demonstrating efficacy of 50% against clinical episodes in this phase IIb study in Mozambique. Therefore the sample size has been calculated to ensure that there is precision around the estimate of effect and that if the true vaccine efficacy is 50% that there is 80% power to detect a lower limit of vaccine efficacy of 15%.

#### Rationale for choice of control vaccines

A vaccine that is of benefit to the control group is preferable to the use of placebo injections and will be more acceptable to all the ethical review bodies for this study (the local Mozambican ethical committee, the co-sponsor’s (MVI) investigational review board [IRB] and the IRB of the University of Barcelona, where the Principal Investigator is affiliated) and the study population.

***Children between the ages of 12 to24 ~~18~~ months***Hepatitis B vaccination (at 2, 3 and 4 months of age in combination with diphtheria-tetanus-pertussis and polio vaccines) was introduced into the EPI schedule of Mozambique in July 2001. It is estimated that 83% of children have received all immunizations by 12 months of age (personal communication from [name]). It is probable that most children under the age of ***24*** ~~18~~ months, at the time the trial is projected to start, will already have received immunization against hepatitis B. Re-immunization with a hepatitis B vaccine would not provide an individual benefit to children under the age of ***24*** ~~18~~ months in this study population. It is therefore proposed to use an alternative control regime in these children: a 7‑valent pneumococcal conjugate vaccine (Prevnar®) will be administered at doses 1 and 3 and a conjugate *Haemophilus influenzae* type b vaccine (Hiberix™) at for the second dose. These vaccines will be administered according to the licensed vaccination schedules for this age group and will thus be of benefit to these children[[19]](#endnote-20),[[20]](#endnote-21).
**(Amended January 17, 2003)**

Acute lower respiratory tract infections (ALRI) are a major cause of mortality and morbidity in children in the developing world, causing about 3 million deaths in children annually[[21]](#endnote-22). Investigation to determine the causative organism is not routine in most of Africa however, many research studies have now been conducted in African centers and have produced consistent results. The most important causes are: *Streptococcus pneumoniae* (the pneumococcus), *Haemophilus influenzae* and the respiratory syncitial virus (RSV)[[22]](#endnote-23). The pneumococcus is the largest single bacterial cause of ALRI in the developing world. Of the more than 90 serotypes of pneumococcus, the 7 serotypes contained within Prevnar® (4, 6B, 9V, 14, 18C, 19F and 23F) are estimated to cover about 67% of invasive infections in Africa[[23]](#endnote-24). Although Prevnar® (Wyeth Ledrele Vaccines) is licensed in several parts of the world, it is only the US that has incorporated pneumococcal conjugate vaccines into their national immunization schedule. Evidence to support a universal recommendation for pneumococcal immunisation by WHO is being sought. Pneumococcal vaccination is expected to substantially reduce the amount of ALRI experienced and vaccine trials are being conducted in South Africa, The Gambia and The Phillipines to confirm this.

WHO recommends Hib immunisation for children. Key evidence supporting this decision was a vaccine trial examining the effect of Hib vaccination conducted in The Gambia. As expected the vaccine was highly protective against invasive Hib disease (95% CI 67-100), but in addition had a vaccine efficacy of 21.1% (95% CI of 4.6-34.9) against all cases of radiologically defined pneumonia.

Acute bacterial meningitis is another important cause of mortality; in total between 100 000 and 500 000 deaths annually17. Survivors frequently are left with a severe permanent disability[[24]](#endnote-25). Of the three major causes of acute bacterial meningitis, *Streptococcus pneumonia*, *Haemophilus influenzae* and *Neisseria menigitidis*, it is the pneumococcus and *Haemophilus influenzae* that account for the cases outside the epidemic peaks 17, [[25]](#endnote-26). Vaccination against Hib is of well-established benefit for the prevention of meningitis[[26]](#endnote-27).

***Children over 24 ~~18~~ months of age***
In children over the age of ***24*** ~~18~~ months, hepatitis B vaccine is proposed as the control vaccine. In Sub-Saharan Africa, HBV infection is endemic leading to, in a proportion of infected subjects, chronic carriage and the complications of chronic liver disease and hepatoma. Thus, the control group would benefit from this vaccine.
**(Amended January 17, 2003)**

#### Rationale for conducting hepatitis B serology in Cohort 2

This study will compare the immunogenicity of a licensed hepatitis B vaccine (Engerix-B™) and RTS,S/AS02A. Immunogenicity data obtained thus far have consistently shown excellent anti-HBs antibody geometric mean titres and derived seroprotection rates, however, no comparisons with commercial hepatitis B vaccines have been performed to date.

A comparison of RTS,S/AS02A with an established hepatitis B vaccine, with respect to anti-HBs antibodies, will be important at this stage in the clinical development before proceeding to infant studies. To avoid giving infants three doses of RTS,S/AS02A and three doses of hepatitis B vaccine in the first year of life in the planned infant studies, it is proposed to assess the feasibility to replace the existing hepatitis B antigen in the EPI vaccination schedule with RTS,S/AS02A.

The quality of the immune response to vaccination with HBsAg (whether in Engerix-B™ or RTS,S/AS02A) cannot be evaluated directly by a neutralisation assay since no such assay is available due to the lack of *in vitro* replication of the hepatitis B virus. Nevertheless, the generation of monoclonal antibodies against various epitopes of HBsAg have allowed the identification of a protective epitope (RF1). The RF1 monoclonal antibody (RF1 mAb) recognises this conformational epitope on peptide 124-137 of the HBsAg. The RF1 antibody has been shown to protect chimpanzees against infection with the virus[[27]](#endnote-28). In the absence of a neutralisation assay for HBV, RF1-like antibodies in serum from vaccinees can be used as a surrogate marker of neutralising capacity and thus provide a qualitative evaluation of the immune response to vaccination. Therefore, RF1-like antibodies will be measured in all subjects in Cohort 2 at screening and then 30 days post third dose.

The rationale for performing serology testing for anti-HBs antibodies in Cohort 2 rather than Cohort 1 is based on the mistrust of venous blood sampling by the community. Whereas the community are accepting of capillary blood sampling by finger prick, they do not readily accept venous sampling of healthy children. Adding venipuncture to a study results in a higher rate of non-compliance. It has been estimated that without venipuncture the dropout rate is 10%, but it rises to 20% for studies including venipuncture. So that venous blood sampling does not jeopardize compliance in children in Cohort 1, children for Cohort 2 will be recruited from Ilha Josina, a site adjacent to but not overlapping the catchment area for Cohort 1.

The additional blood volumes needed for the hepatitis B serology will require venipuncture at some time points. Therefore, to minimise the total number of children enrolled in the this phase IIb study, this endpoint is proposed for a separate cohort (Cohort 2) and a non-compliance rate of 20% has been applied to the sample size for this cohort only.

#### Assessment of vaccine reactogenicity

Adverse event data will be collected on ***990*** ~~960~~ recipients of the paediatric dose (0.25 ml dose level) of RTS,S/AS02A in the course of this phase IIb trial in 1-4 year old children. This will allow for the reactogenicity profile of the vaccine to be defined with higher precision than previously done in the smaller paediatric phase I studies (Malaria-015 and Malaria-020).
**(Amended January 17, 2003)**

The proposed schedule in this trial is 0,1,2 months as opposed to 0,1,3 months in the phase I studies in the Gambia (Malaria-015 and 020). Based on results of a previous study in malaria-naïve adults, which evaluated vaccination at 0,1,3 months versus 0,7,28 days and showed that schedule had no effect on the reactogenicity profile, no significant impact on reactogenicity is expected after vaccination at 0,1,2 monthsError: Reference source not found. In the paediatric phase I study in 1-5 year-olds, a slight trend with increasing dose level and number of doses was only seen for the local symptom of swelling and the general symptom of irritability/fussiness (please see section 1.1.1 for a summary of the data). Although the study children are not expected to react any differently to the Gambian children, a blinded review of safety and reactogenicity data after two doses from the phase I trial (using a 0,1,2 month vaccination schedule) in 1-4 year-old children in Manhiça (Mozambique) will be performed before proceeding with this phase IIb study.

The control vaccines are all licensed vaccines with established reactogenicity profiles, thus the adverse event rate in the recipients of these vaccines is expected to be similar to previous experience with these vaccines. However, in this developing community in Mozambique, the acute febrile illnesses of childhood, particularly respiratory tract infections and malaria, occur frequently. Many of these common viral and bacterial infections will be seen with equal frequency among the recipients of hepatitis B vaccine and RTS,S/AS02A and the comparison with the control group is useful to distinguish vaccine effects from those due to intercurrent illness. However, those younger children, who receive immunization against pneumococcal and haemophilus disease, could be expected to be protected against some of the most common infections of childhood. With the small numbers enrolled in this group, it is unlikely to reach levels of statistical significance.

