## Treatment allocation and randomization

Study subjects will not be randomly assigned to Cohorts 1 and 2 instead the required number of subjects from Manhiça town will enrolled for Cohort 1 and from Ilha Josina area for Cohort 2.

A randomization list will be created at GSK Biologicals to allocate subjects between the two groups (malaria vaccine group or control vaccine group) by block randomization. Vaccines (RTS,S/AS02A, Engerix-B™, Prevnar® and Hiberix™) will be numbered accordingly and dispensed to the site in individual boxes labeled with unique study numbers.

Study numbers ***0101‑0700 ~~400~~*** will be provided for the children less than ***24*** ~~18~~ months of age and study numbers ***0701‑2300 ~~0401‑2200~~*** will be provided for those children older than ***24*** ~~18~~ months of age. On the day of first vaccination, children will be allocated according to their age, sequentially in order of their arrival, to the next study number. For children of less than ***24*** ~~18~~ months, the numbering will start at ***0101*** and for children of ***24*** ~~18~~ months and over, the numbering will start at ***0701 ~~0401~~***. A total of ***1980*** ~~1920~~ children will be enrolled. When this number is reached, enrollment will cease. Because ***495*** ~~240~~ children are predicted to be less than ***24*** ~~18~~ months of age but this number is not known precisely until after screening results are available, over-randomization is necessary and ***2200*** ~~2100~~ numbers will be prepared for ***1980*** ~~1920~~ children. Thus, over-randomization will allow some flexibility at the time of enrolment.

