**(Amended January 17, 2003)**

This study will compare the immunogenicity of a licensed hepatitis B vaccine (Engerix-B) and RTS,S/AS02A. A non-inferiority approach will be used to calculate the power of the study for the comparison of seroprotection rates and geometric mean titres of anti-HBs antibodies. From census information gathered by CISM, approximately ***25%*** ~~12.5%~~ of the population will be less than ***24*** ~~18~~ months of age. Therefore the assessment of the anti-HBs antibody immune response will be based on approximately 248 evaluable subjects (124 subjects per group). This sample size will have ***89%*** ~~95%~~ power at a ***2.5%*** ~~5%~~ significance level using a one-sided equivalence test of proportions when the proportion that are seroprotected in the control group (subjects vaccinated with Engerix-B™) is at least 0.95 and the proportion in the RTS,S/AS02A group (subjects of ***24*** ~~18~~ months of age or more) is 0.95 and the maximum allowable difference between these proportions that still results in equivalence (the range of equivalence) is 0.10 (PASS 2000,one sided equivalence test of proportions, alpha = ***2.5%*** ~~5%~~).

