### Analysis of safety

All safety and reactogenicity analyses will be performed for the Total Cohort.

The overall percentage of subjects reporting any adverse event after vaccination will be tabulated with exact 95% confidence intervals, by type of adverse event; by severity (any grade, grade 3 only); by relationship (No, Yes, respectively).

The overall percentage of doses for which any adverse event is reported after vaccination will be tabulated with exact 95% confidence intervals, by type of adverse event; by severity (any grade, grade 3 only); by relationship (No, Yes, respectively).

The proportion of subjects with at least one report of unsolicited adverse event, classified by MedRA, reported up to 30 days after vaccination, will be tabulated. The same tabulation will be performed for unsolicited adverse events with relationship to vaccination.

Serious adverse events and discontinuation due to adverse event(s) will be described in detail.

Serum ALT, bilirubin creatinine levels, hematocrit values and body weight that are outside of the reference ranges will be described.

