Appendix G: Vaccine Supplies, Packaging and Accountability

It is under no circumstances permitted to use supplies for purposes other than those specified in the protocol.

1. Vaccine supplies

The investigator will be supplied by the sponsor the following amounts of numbered doses of study vaccines, sufficient to administer 3 dose(s) to all subjects as described in the present protocol:

- ***3300*** ~~3150~~ doses of the RTS,S/AS02A malaria candidate vaccine
  RTS,S/AS02A will be supplied such that the reconstituted vaccine volume will be 0.5 ml per vial. The contents of each vial will be used to prepare one paediatric dose (0.25 ml dose volume) only.
- ***2400*** ~~2700~~ doses of the Hepatitis B vaccine (Engerix-B™)
- ***300*** ~~150~~ doses of *Haemophilus influenzae* type b vaccine (Hiberix™)
- ***600*** ~~300~~ doses of 7-valent pneumococcal conjugate vaccine (Prevnar®)

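### Safety tables pool two control regimens, one expected to prevent common infections; the small-numbers reason for setting this aside was not revisited when Amendment 2 doubled that stratum

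*Supplement*

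**What the plan says.** Section 1.2.2.6 presents the control group as the means of telling vaccine effects from intercurrent illness. It expects common infections to be equally frequent in hepatitis B and RTS,S/AS02A recipients, then makes an exception: "those younger children, who receive immunization against pneumococcal and haemophilus disease, could be expected to be protected against some of the most common infections". It closes the matter with "With the small numbers enrolled in this group, it is unlikely to reach levels of statistical significance".

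Section 1.2.2.4 explains that the under-24-month control vaccines were chosen for their benefit against pneumonia and meningitis. On Hib vaccine it cites a trial which "in addition had a vaccine efficacy of 21.1% (95% CI of 4.6-34.9) against all cases of radiologically defined pneumonia".

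Amendment 2 (January 17, 2003) moved the age cut-off from 18 to 24 months. In section 6.4 the predicted stratum size changed: "Because *495* ~~240~~ children are predicted to be less than" the cut-off. In section 10.6.2 the share changed: "approximately *25%* ~~12.5%~~ of the population will be less than" that age.

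Section 10.7.3 states: "All safety and reactogenicity analyses will be performed for the Total Cohort". It then lists overall percentages of subjects and of doses by event type, severity and relationship, and says serious adverse events will be described in detail. It names no split by age stratum or control regimen.

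**The concern.** The control arm is two comparators. At 24 months and over it is Engerix-B, which is not expected to affect respiratory or bacterial illness. Under 24 months it is Prevnar at doses 1 and 3 and Hiberix at dose 2, chosen because they should reduce such illness. In that stratum, fewer infections among controls look the same as more infections among RTS,S/AS02A recipients.

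The protocol recognised this and gave a reason for taking no action. That reason was the size of the group, which Amendment 2 then doubled. The amendment did edit section 1.2.2.6 (960 recipients became 990) but left this sentence as it was.

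The imbalance can also persist. Serious adverse events are recorded until 19 months after the last dose (section 8.1), and RTS,S/AS02A recipients in the younger stratum are offered Prevnar and Hiberix only at month 21 (section 5.2.12).

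A lesser consequence is that solicited reactions in the pooled control column are a mixture: about a quarter of control doses are Prevnar at doses 1 and 3, and about a quarter are Hiberix at dose 2.

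**Working it through.** **Reproducing the plan's figures.** Share times total enrolment: 0.25 × 1980 = 495 now, and 0.125 × 1920 = 240 before. Both match section 6.4. Cross-check on supplies: study numbers 0101–0700 are 600 numbers, half of them control, so 300 Hiberix doses (one each) and 600 Prevnar doses (two each). Both match Appendix G.

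**Who is in the group.** The 495 covers both arms. With 1:1 allocation, 495/2 = 247.5, about 248 controls; before, 240/2 = 120. These controls are 247.5/990 = 25% of the control arm.

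**Distortion of the pooled comparison.** Suppose RTS,S/AS02A has no effect on the infection. Let e be the control-vaccine benefit, s the younger stratum's share of children, and k the incidence in younger relative to older children without any control benefit. The younger stratum's share of events is w = sk/(sk + 1 − s), and the apparent relative risk is 1/(1 − we). The only value of e in the documents is 0.211; k is not given and is assumed.

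| k (assumed) | w before | RR before | w after | RR after |
|---|---|---|---|---|
| 1 | 0.125 | 1.027 | 0.250 | 1.056 |
| 2 | 0.222 | 1.049 | 0.400 | 1.092 |
| 3 | 0.300 | 1.068 | 0.500 | 1.118 |

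For example, with k = 1 after the amendment: 1/(1 − 0.25 × 0.211) = 1/0.94725 = 1.056. With e assumed at 10% or 40% and k = 1, the figure after the amendment is 1.026 or 1.111.

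**Within the younger stratum**, before or after: 1/(1 − 0.211) = 1.27.

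**Apparent excess in events.** Children per arm in the stratum × event rate p × e. The documents give no p, so it is assumed.
- p = 10%: 247.5 × 0.10 × 0.211 = 5.2 (before: 120 × 0.10 × 0.211 = 2.5).
- p = 30%: 247.5 × 0.30 × 0.211 = 15.7 (before: 7.6).
- For serious lower respiratory events at p = 5% to 15%: 2.6 to 7.8. With an assumed e of 40%: 5.0 to 14.9.

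**Chance of statistical significance** (two proportions, normal approximation, two-sided 5%, e = 21.1%):
- Within the stratum, the probability rises from 8% to 13% at p = 10%, and from 20% to 36% at p = 30%.
- In the pooled comparison of 990 per arm it is 6% at p = 10% and 12% at p = 30%.
- Only under a strong assumption (e = 40%, p = 30%) does the within-stratum figure become high: 59% before, 88% after. The pooled figure is then 32%.

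**The case against.** Five points have force.

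- **Analysis plan not shown.** Sections 6.5.1 and 10 leave detail to a reporting and analysis plan, which could contain a split by age or regimen. The Total Cohort sentence in 10.7.3 sets the analysis population; it does not forbid stratified tables. Pooling is inferred from the two-group definition in 6.4 and the absence of any split. This limits the point but does not remove it: the protocol itself decides that the issue can be ignored, on a premise its own amendment changed. Where regimen matters for anti-HBs, section 10.6.2 does restrict the comparison to children of 24 months or more.
- **The significance remark largely survives.** At a 21.1% benefit the probabilities above stay low. That stands. But 10.7.3 is descriptive and plans no between-arm test, and lack of significance does not remove a shift in one direction.
- **Safeguards exist.** Serious events are described individually, with causality and contributing factors assessed (section 8.3) by blinded investigators in the double-blind phase. These help with single cases; they do not correct a comparison of frequencies.
- **DSMB.** A reader might infer that the DSMB would be misled after each dose. Section 5.2.4 says those reviews use blinded data, so no arm comparison is described there. The concern is with the final tables.
- **Reactogenicity aim.** The stated aim is to define the RTS,S/AS02A profile in 990 recipients, and the control mix does not alter that. The mixture matters only when the two columns are compared.

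**Conclusion.** The point holds as a moderate one. The reason given in 1.2.2.6 rests on a group half its present size, and the safety section specifies no table in which the expected control-vaccine benefit could be seen. At the one benefit figure in the documents, and with equal incidence across ages, the null relative risk is about 1.06 pooled (1.03 before the amendment) and about 1.27 in the younger stratum.

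This assumes that a Hib-vaccine result against radiological pneumonia carries over to the events counted here. The documents give no combined pneumococcal and Hib benefit and no event rates, and Hiberix is given only at the second vaccination.

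Three stronger readings are tempting and not supported. The documents do not show that a false harm signal will occur: the protocol says protection could be expected, and the pooled effect is small. They do not show that the control group fails in its purpose: three quarters of controls receive Engerix-B. And 495 is not the number of children given Prevnar and Hiberix; that is about 248.

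**What to change.** In section 10.7.3, add tables of solicited, unsolicited and serious adverse events by arm within each age/control stratum, beside the overall tables: under 24 months against Prevnar/Hiberix, by dose, and 24 months or older against Engerix-B. State that respiratory and meningitis serious adverse events will be interpreted in both strata with the possible control-vaccine benefit in mind, and that neither stratum takes priority. Reading the Engerix-B stratum first would discount a true signal in the youngest children.

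In section 1.2.2.6, replace the small-numbers statement with the current figures (about 248 controls; 495 children in the stratum across both arms), and add that lack of significance does not remove the bias.

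The cost is a set of extra tables from data already collected. The separate number ranges (0101–0700 and 0701–2300) already define the strata, so each comparison is randomised. Intervals within strata will be wider, most of all with about 248 per arm in the younger one.
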